# Palliative long-term abdominal drains versus repeated drainage in individuals with untreatable ascites due to advanced cirrhosis: study protocol for a feasibility randomised controlled trial

**DOI:** 10.1186/s13063-018-2779-0

**Published:** 2018-07-27

**Keywords:** Ascitic fluid, End-stage liver disease, Paracentesis, Permanent indwelling peritoneal catheter, Palliative care, Healthrelated quality of life, Quality-adjusted life years, Healthcare economics

## Abstract

**Background:**

UK deaths due to chronic liver diseases such as cirrhosis have quadrupled over the last 40 years, making this condition now the third most common cause of premature death. Most patients with advanced cirrhosis (end-stage liver disease [ESLD]) develop ascites. This is often managed with diuretics, but if refractory, then the fluid is drained from the peritoneal cavity every 10–14 days by large volume paracentesis (LVP), a procedure requiring hospital admissions. As the life expectancy of patients with ESLD and refractory ascites (if ineligible for liver transplantation) is on average ≤ 6 months, frequent hospital visits are inappropriate from a palliative perspective. One alternative is long-term abdominal drains (LTADs), used successfully in patients whose ascites is due to malignancy. Although inserted in hospital, these drains allow ascites management outside of a hospital setting. LTADs have not been formally evaluated in patients with refractory ascites due to ESLD.

**Methods/design:**

Due to uncertainty about appropriate outcome measures and whether patients with ESLD would wish or be able to participate in a study, a feasibility randomised controlled trial (RCT) was designed. Patients were consulted on trial design. We plan to recruit 48 patients with refractory ascites and randomise them (1:1) to either (1) LTAD or (2) current standard of care (LVP) for 12 weeks. Outcomes of interest include acceptability of the LTAD to patients, carers and healthcare professionals as well as recruitment and retention rates. The Integrated Palliative care Outcome Scale, the Short Form Liver Disease Quality of Life questionnaire, the EuroQol 5 dimensions instrument and carer-reported (Zarit Burden Interview) outcomes will also be assessed. Preliminary data on cost-effectiveness will be collected, and patients and healthcare professionals will be interviewed about their experience of the trial with a view to identifying barriers to recruitment.

**Discussion:**

LTADs could potentially improve end-of-life care in patients with refractory ascites due to ESLD by improving symptom control, reducing hospital visits and enabling some self-management. Our trial is designed to see if such patients can be recruited, as well as to inform the design of a subsequent definitive trial.

**Trial registration:**

ISRCTN, ISRCTN30697116. Registered on 7 October 2015.

**Electronic supplementary material:**

The online version of this article (10.1186/s13063-018-2779-0) contains supplementary material, which is available to authorized users.

## Background

UK deaths due to chronic liver disease such as cirrhosis have quadrupled over the last 40 years, making this condition the third most common cause of premature death [1]. Ascites — an abnormal accumulation of fluid in the peritoneal cavity — is present in up to 90% of patients with advanced cirrhosis [2, 3], resulting in frequent hospitalisations due to debilitating episodes of pain and breathlessness. In the early stages, this condition can be managed using diuretic therapy, but as the condition progresses (end-stage liver disease [ESLD]) the ascites becomes unresponsive to medical treatment. In the absence of liver transplantation, a diagnosis of refractory ascites confers a median life expectancy of ≤6 months [3–5].

End-of-life care in patients with ESLD and refractory ascites has not been a research priority. More than 70% of patients with ESLD die in hospital [6], a figure substantially — and in our view unacceptably — higher than that of 40% for patients with terminal cancer [7]. The most common palliative management for refractory ascites due to ESLD is large volume paracentesis (LVP), performed every 10–14 days [3]. This involves a costly 24–48 h hospital admission, insertion of a temporary abdominal drain and removal of up to 15 L of ascitic fluid over 4–6 h. There is simultaneous administration of intravenous 4.5% or 20% (w/v) human albumin solution, 8–10 g per 1 L of ascitic fluid removed [3]. Consequently, patients often delay the hospital visits until their ascites is tense and painful [8], thus reducing their quality of life (QOL) [9]. Individuals with refractory ascites often have contraindications to alternative invasive procedures such as the transjugular intrahepatic portosystemic shunt (TIPS) [10] and/or the automated low-flow ascites (ALFA) pump [11].

There are additional concerns related to this specific patient group. We do not know whether such individuals would be able or even willing to participate in an RCT, given their potentially higher prevalence of alcohol and substance misuse and other psychosocial issues. Similarly, there is uncertainty as to the most appropriate assessment tools and outcome measures. Finally, given the complex end-of-life care needs of this cohort, concerns remain to patients, carers and healthcare professionals (HCPs) over a strategy that moves care away from the hospital to the community. To address these issues we have designed a feasibility study to inform the development of a subsequent definitive RCT.

## Methods/design

### Aim, design and setting of the study

The aim of this study is to assess the feasibility of conducting a future RCT of the safety, clinical effectiveness and cost-effectiveness of refractory ascites management using the LTAD against current standard of care (LVP) in patients with ESLD when liver transplant is not an option. This document is based on v6.0 of the protocol (13 October 2017). This multicentre trial has been designed in accordance with phase 2 of the Medical Research Council (MRC) Complex Interventions Framework [17] and the Method Of Researching End of Life Care guidance (MORECare) [18].

This feasibility RCT is being conducted both at a hospital (the Royal Sussex County Hospital [RSCH], Brighton, Sussex, UK and the Princess Royal Hospital [PRH], Hayward’s Heath, Sussex, UK, both part of the Brighton and Sussex University Hospital [BSUH] National Health Service [NHS] Trust; Worthing Hospital, Worthing, Sussex, UK [Western Sussex NHS Foundation Trust], Plymouth Hospitals NHS Trust, Plymouth, UK, Blackpool Victoria Hospital, Blackpool, UK [Blackpool Hospitals NHS Foundation Trust] and Southampton General Hospital, Southampton, UK [University Hospital Southampton NHS Foundation Trust]) and in a community setting (The Sussex Community Trust). Those randomised to the LTAD will be followed up in the community. This 3-year study is planned to run from September 2015 until September 2018.

### Characteristics of participants

Patients will be identified from acute medical units, outpatients and gastroenterology and hepatology wards. They will be approached for the study at the participating centres by the research team after having been identified by the local medical team as being potentially eligible.

### Inclusion criteria

The inclusion criteria are as follows:Age ≥ 18 years, with no upper age limitUntreatable (refractory) ascites defined as:Ascites that is unresponsive to fluid and sodium restriction and high-dose diuretic treatment (spironolactone 400 mg/day and/or furosemide 160 mg/day) and/or intolerance of diuretics [19, 20]Ascites that recurs rapidly after LVP (requiring one or more LVP/month).Child-Pugh score [21] of ≥ 9 unless specifically decided by the medical team that they are to receive only palliative treatmentRegistered with a general practitioner (GP) in the Community Trusts serving the participating centresAbility to speak, read and understand EnglishCapacity to give written informed consent as assessed by using a Capacity to Consent Checklist (see Additional file 1)

### Exclusion criteria

The exclusion criteria are as follows:Loculated or chylous ascitesPresence of > grade 1 hepatic encephalopathy (specified by West Haven Criteria [22])Evidence of active infection, which in the Investigator’s opinion would preclude insertion of an LTAD, e.g. bacterial peritonitis. Such patients could be reconsidered for inclusion in the trial if infection has been successfully treatedEligible for liver transplantation, in the opinion of the hepatology multidisciplinary team (MDT) and according to national guidelines [23]Psychosocial issues which, in the medical team’s opinion, would preclude engagement with the trial, such as posing a risk to the safety of oneself or the research team

As this is a feasibility study, we will not specifically exclude patients based on abnormal haemostasis measurements. Consistent with local practice, those individuals with a platelet count of < 50 × 10^9^ and/or an international normalised ratio (INR) of > 1.7 will be given blood and/or clotting products prior to receiving an LTAD or LVP.

Potential participants can be considered for inclusion in this trial even if they are currently participating in another research study, as long as their medical team are confident that participation in the current trial would be logistically feasible and not unduly onerous for the participants.

While we would prefer that potential carers/consultees are identified for each participant, their absence will not preclude study participation.

### Consent

Suitable participants will be identified by the usual medical teams. A research team member (to include Chief Investigator [CI], co-investigators, Principal Investigators [PIs], nurse and research fellow) will provide patient information sheets (PISs) to potential research participants and give an explanation about the study including ascites management. Patients will be provided at least 48 h to read the PIS. If willing, consent will be obtained in hospital by a research team member. If the research team is the usual medical team, to avoid any potential conflict of interest, potential participants will be discussed at the weekly liver multidisciplinary meeting (MDM). Capacity to give informed consent will be carefully assessed (see inclusion criteria). In the event that capacity is lost during the trial, the participant’s nominated consultee will be approached to determine whether the participant should continue in the study. If a consultee has not been nominated or is unavailable, then the participant’s usual medical consultant (independent from the research team) will be consulted to decide whether it is in the participant’s best interests to continue in the study.

### Randomisation

Patients who fulfil the inclusion and exclusion criteria and give written informed consent to participate in this trial will be randomised on a 1:1 basis to either Group 1: LTAD or Group 2: LVP (current standard of care). The allocations will be made by minimising on (1) centre, (2) Child-Pugh score and (3) gender. No stratification will be utilised. Minimisation will be implemented using an independent system hosted at King’s Clinical Trials Unit (KCTU). Patients will be enrolled by the research team member, who will log into the web-based system and enter patient ID number, recruiting site, gender and Child-Pugh score. The system will automatically generate a confirmation email informing the research team of the outcome of allocation.

Patients will be followed up for 12 weeks. With the participants’ agreement we will inform their GPs about their participation in the trial.

### Interventions

#### Group 1: LTAD

There are two LTADs currently available in the UK: the PleurX™ (UK Medical Ltd., Basingstoke, UK [24]) and the Rocket® (Rocket Medical, Watford, UK [25]). We have chosen to use the Rocket device (Fig. 1) [25] primarily because our local clinicians and community nursing teams are already familiar with it. Rocket Medical already has an established training and support programme for local community nurses and care homes. In addition, our earlier experience [26] suggests that the Rocket devices are easier to insert than the PleurX™ devices and that they require less expensive consumables that can currently be prescribed by community practitioners.

**Fig. 1 Fig1:**
[figure not shown]
Rocket Medical Long-Term Abdominal Drain in situ [25]

#### Procedure for insertion of LTAD

Insertion of the LTAD will be performed in hospital in a side room, using bedside ultrasound guidance. Insertion will only be performed if, within the week leading up to planned LTAD insertion, haemostatic function (including INR and platelet count) has been checked and blood products administered as necessary. Where INR is > 1.7, patients will receive up to two volumes of fresh frozen plasma (FFP), transfused according to patient weight and INR, immediately prior to drain insertion. Where the platelet count is ≤ 50 × 10^9^, patients will be given one to two pools of platelets immediately prior to insertion of the drain.

To ensure consistency, it would be ideal that all LTADs are inserted at one site (RSCH), but if this is not possible due to patient preference or logistic issues, they will be inserted at local sites, usually by an interventional radiologist.

The Rocket® LTAD will be inserted using a combination of tunnelled and Seldinger technique as stated in the Rocket® information sheet [25]. After confirming the location of the insertion site using bedside ultrasound and skin preparation with Chloraprep™ (chlorhexidine gluconate and isopropyl alcohol), a local anaesthetic (up to 10 ml 1% or 2% lidocaine) will be administered at the incision site and along the proposed tunnel tract. A small incision is made where the catheter will enter the abdominal cavity. The introducer needle will be inserted through the incision into the peritoneal cavity and a guide wire is passed through the needle, which will then be removed. A second incision (exit site) will be made approximately 5 cm medial from the first, where the catheter will exit the tunnel. The catheter will be tunnelled from exit site incision to the first incision site with the tunneller, making sure that the cuff is midway between the first and second incision sites. A split-sheath dilator will then be passed over the guide wire, and the inner dilator and guide wire removed, leaving the split sheath in situ.

The tunneller is then removed from the catheter, which is then passed through the split sheath, separating the split sheath and ensuring that all of the catheter is contained within the peritoneum. The last piece of the split sheath is then removed. The catheter is then adjusted along the tunnel, so the cuff moves towards the exit site, ensuring that any kinks are removed from the catheter. Finally, both incision sites will be sutured (avoiding the catheter) and a dressing applied.

Participants will receive antibiotic prophylaxis (ciprofloxacin 500 mg/day) or an equivalent antibiotic (if there is a contraindication to ciprofloxacin), dependent on local practice.

We will provide guidance to the participant and carer (where present) on how to use the LTAD, based on the information previously supplied in the PIS. Participants will also be given an information sheet provided by Rocket Medical [25]. Participants will be referred to their community nursing service. A Rocket Medical discharge letter will be sent to their GPs and the community nursing team. Rocket Medical will also be informed so that they can organise any further support/training for patients, carers and community nurses. In addition, we will arrange for drainage bags to be delivered directly to the participant’s usual place of residence on request by the community nurses.

The community nurses will visit the participants in their homes and either perform the drainage procedure themselves or supervise the drainage of ascites. The frequency of these visits will depend on the participant’s ascites-related symptoms, but work in ascites due to malignancy [12, 27] indicates that two to three visits each week are most commonly required, with approximately 1–2 L of ascites being drained each time. It is recommended that the drainage frequency not exceed three times per week. In the event that participants and/or carers wish to perform self-drainage, they will be trained to do so by the community nurse.

The Integrated Primary Care Team (IPCT) will closely monitor trial participants allocated to the LTAD arm. We expect that this will happen two to three times a week if the community nurses are performing ascitic fluid drainage.

For participants who live in a care home or move to a care home (with or without nursing), the follow-up procedure would be the same as for patients who live at home. In such cases we would seek approval from the care home managers. For those requiring hospice care, this would be a temporary stay, since hospices do not generally provide long-term care. Again, permission will be sought from the hospice team to visit the participants for follow-up and only if such visits remain acceptable to the participants.

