#### Group 2 standard of care (LVP)

Participants randomised to LVP [3], the current standard of care, will be admitted to hospital as either a self-referral or via their GP, whichever is current local practice. They will undergo LVP as clinically indicated. LVP involves the insertion of a peritoneal drain for up to 6 h and removal of up to 15 L of ascites. If the total volume of fluid to be removed is > 5 L, intravenous 4.5% or 20% (w/v) human albumin solution, 8–10 g per 1 L of ascitic fluid removed, will be administered [3].

As with Group 1, participants will receive antibiotic prophylaxis (ciprofloxacin 500 mg once a day or an equivalent antibiotic (if there is any contraindication to ciprofloxacin), dependent on local practice).

For both groups there will be two weekly visits with a research team member for questionnaire-based and clinical assessments as well as routine clinical blood samples (as discussed in subsequent sections). We anticipate that these two weekly contacts will improve adherence to the protocol.

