### Schedule of assessments

The research team member will visit participants at home every 2 weeks for questionnaire-based and clinical assessments (see the subsequent section) as well as collection of routine clinical blood samples. The amount and frequency of drainage and other pertinent observations will be recorded by community nurses in a formal study diary, as is the case when the LTAD is used in patients with ascites due to malignancy. The research team member will train and advise the community nurses and participants on data collection to reduce the possibility of missing data. See Fig. 2 and the Standard Protocol Items: Recommendations for Interventional Trials (SPIRIT) schedule (Fig. 3).

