### Suspected unexpected, serious adverse reactions (SUSARs)

This category will include all SARs that in the opinion of the CI are directly related to the intervention and are not listed as a known (expected) SAR. All SUSARs that occur between insertion of the LTAD and 3 months post insertion or death, whichever is earlier, will be recorded on the eCRF and emailed/faxed to the BSCTU immediately, at least within 24 h of the research team becoming aware in accordance with the BSCTU Safety Reporting SOP. The REC will be notified of any SUSAR to the study intervention by the BSCTU. For each SUSAR, all relevant information will be collected, and the SUSAR will be followed up until resolved or a final outcome reached.

The CI will have direct and ultimate responsibility for reviewing all reported SARs and SUSARs and will ensure that the BSCTU reports these appropriately according to the BSUH SOP on Safety Reporting in Non-Clinical Trial of an Investigational Medicinal Product (CTIMP) studies.

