**Fig. 4 Fig4:**
[figure not shown]
Consort flow chart

Descriptive statistics will be used to summarise and compare the quantitative outcome measures to include (1) complication rates: failed insertion, drain leakage or blockage, cellulitis, bleeding, pain at site of insertion not controlled by analgesia, peritonitis, sepsis and death (the latter two only if directly related to the LTAD), (2) symptoms: IPOS, QOL (SF-LDQOL, EQ-5D-5 L) [28, 33–35] and (3) carer burden [36, 37] for each arm. Means and standard deviations will be determined for normally distributed outcomes and medians and interquartile ranges for skewed outcomes at the different time points and at the end of the study. Analyses will use all available cases following intention-to-treat principles. We will calculate 95% confidence intervals for parameter estimates as appropriate. Prior to the analysis of the data, a detailed statistical analysis plan will be written and signed off.

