#### Qualitative data analysis

If purposive sampling is not feasible, the proportion of participants choosing to participate in qualitative interviews will be noted. Interviews will be audio recorded and labelled using the same anonymous study number as the intervention component of this study. The same number will be used so that in the event of a participant reporting a serious concern about his/her condition or care, the qualitative researcher can raise this concern with the patient’s clinician. In this unlikely event, the researcher will inform the patient of the need to convey this information to the clinician. The qualitative researcher will have access to the clinical study data of the individual if needed.

Thematic analysis supported by qualitative software (NVivo) [45] will be used to extract overarching themes from the interviews to capture patients’ experiences and beliefs. Utilising the process of triangulation [46], the findings of the qualitative arm will be used to inform the quantitative results, particularly in the context of QOL and experience of end-of-life care provision.

Data will be analysed in a blinded manner. However, the research team members collecting information from the patients will always be aware of their allocation since a high level of scrutiny is necessary to ensure that there are no safety events in the LTAD group. Our service users were also insistent that participants not engage with multiple members of the research team, further excluding blinded data collection.

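### LTAD patients are seen more often than LVP patients, so the by-arm comparison of complications is likely to pick up more of the brief harms common to both arms under LTAD

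*Protocol article*

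**What the plan says.** The section on LTAD insertion states: "The Integrated Primary Care Team (IPCT) will closely monitor trial participants allocated to the LTAD arm". The frequency is conditional: "We expect that this will happen two to three times a week if the community nurses are performing ascitic fluid drainage". The same section allows self-drainage: "In the event that participants and/or carers wish to perform self-drainage, they will be trained to do so by the community nurse".

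Schedule of assessments adds a diary: "The amount and frequency of drainage and other pertinent observations will be recorded by community nurses in a formal study diary". That sentence names no arm, but drainage by community nurses belongs to the LTAD arm only.

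The section on Group 2 gives the contact common to both arms: "For both groups there will be two weekly visits with a research team member for questionnaire-based and clinical assessments". LVP patients otherwise come to hospital for drainage when it is needed. The Background puts this at every 10–14 days, with a stay of 24–48 h.

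Safety monitoring has every adverse event recorded on the eCRF, however it was found. Statistical analysis then says: "Descriptive statistics will be used to summarise and compare the quantitative outcome measures to include (1) complication rates". The list that follows runs from failed insertion to death and is to be given for each arm. Under Qualitative data analysis, the reason offered for unblinded data collection is that "a high level of scrutiny is necessary to ensure that there are no safety events in the LTAD group".

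**The concern.** A harm that resolves quickly and needs no admission is counted only if someone sees it or the patient reports it later. One arm has many more occasions on which it can be seen, and the data collectors know the allocation and have been told where to look harder. The all-source counts then go into a comparison between arms. At equal true rates, the arm examined more often tends to show more such events.

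Extra scrutiny of a device that is new in this population is right for safety. The difficulty is only in reading the resulting between-arm difference. Complication rates are a stated objective of the study, and the Background gives bleeding and infection as the reasons why these drains have not been assessed in ESLD. A difference caused by surveillance could therefore colour the case for the definitive trial.

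**Working it through.** The plan gives no figure for ascertainment. Its sample size reproduces: 12/(1 − 0.5) = 24 per arm, 48 in total. The point does not depend on it.

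**Contacts over 12 weeks (84 days)**
- LTAD with nurse drainage: 2–3 per week × 12 = 24–36, plus 84/14 = 6 research visits, total 30–42.
- LVP: 6 research visits plus 84/14 = 6 to 84/10 = 8.4 admissions, total 12–14.4. Usual community nurse visits would add to this.
- Ratio: 30/14.4 = 2.1 to 42/12 = 3.5.

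**Chance that a harm is seen while present.** Assume that onset is uniform in time, that contact schedules are independent, that the true rate is the same in both arms, and that nothing is recalled afterwards. For a harm lasting d days and contacts of length s every v days, one schedule catches it with probability min(1, (d + s)/v). Combining schedules:

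P(seen) = 1 − Π[1 − min(1, (d + s)/v)]

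Inputs:
- Research visit: v = 14, s = 0.
- Nurse visit: v = 7/2 = 3.5 or 7/3 = 2.33, s = 0.
- LVP admission: v = 14 with s = 1 day, or v = 10 with s = 2 days (24–48 h stays).

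For d = 3:
- LTAD, two nurse visits a week: 1 − (1 − 3/3.5)(1 − 3/14) = 0.89. With three a week: 1.00.
- LVP every 14 days: 1 − (1 − 3/14)(1 − 4/14) = 0.44. Every 10 days: 1 − (1 − 3/14)(1 − 5/10) = 0.61.

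| Harm lasts | LTAD, nurse drainage | LVP | LTAD, research visits only |
|---|---|---|---|
| 1 day | 0.34–0.47 | 0.20–0.35 | 0.07 |
| 3 days | 0.89–1.00 | 0.44–0.61 | 0.21 |
| 7 days | 1.00 | 0.79–0.95 | 0.50 |
| 14 days | 1.00 | 1.00 | 1.00 |

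The last column is the limiting case of a self-draining patient with no nurse contact, d/14. For 1-day harms the lowest LTAD figure (0.34) is slightly below the highest LVP figure (0.35), because a two-day stay every 10 days is itself close observation.

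**Scale in patients.** If the true risk were 25% in both arms (an assumption), 3-day harms would appear as 0.25 × 0.89 to 0.25 × 1.00 = 22–25% in LTAD, against 0.25 × 0.44 to 0.25 × 0.61 = 11–15% in LVP. With 12 analysable patients per arm, that is about 3 patients against 1 or 2.

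**The case against.** The strongest reply is that the contact gap is a best case and the affected part of the list is short.

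- **Contacts.** The nurse frequency is an expectation tied to nurse drainage, and self-drainage is allowed. The health economics section expects community nurse visits in both groups, and Clinical follow-up adds a community nurse referral whenever a specialist referral is made. This stands, so 30–42 is an upper range and 12–14 may be low.
- **Model.** LVP bleeding and pain may cluster around a procedure done in hospital, and both arms have a clinical assessment every two weeks at which events can be recalled. Both points reduce the gap by an amount the documents do not allow one to compute.
- **List.** Failed insertion and drain leakage or blockage are device-specific. Sepsis and death count only if attributed to the LTAD. Pain is listed only where analgesia fails, and bleeding is not graded. This also stands and narrows the point to a few items.
- **Decisions.** The comparison is descriptive, and the only complication criterion for study success, LTAD removal below 10%, concerns one arm. At 12 per arm, sampling error is large: the exact 95% interval for 3/12 is about 5–57%.
- **SAP and eCRF.** Source fields and table rules often sit there. But the protocol itself fixes the unequal contact, the all-source recording and the comparison, and events can be separated by source later only if the source was captured.

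A reader might also infer that the LTAD arm has a longer window for harms, from "All SUSARs that occur between insertion of the LTAD and 3 months post insertion or death, whichever is earlier". The documents do not support this. That window governs reporting of unexpected reactions, which by definition lie outside the expected list that the compared complications largely follow, and follow-up is 12 weeks for all patients. Nor can it be said that LVP always misses a material share of week-long harms: the missed share is 5–21% before recall.

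**Conclusion.** The point holds in a limited form. Short-lived harms that can occur in either arm and do not lead to admission, mainly cellulitis, minor bleeding and pain, are likely to be found more often under LTAD at equal true rates. Where nurses drain and nothing is recalled, the chance of detection is about 1.5 to 2.3 times as high for a 3-day harm (0.89/0.61 to 1.00/0.44) and 1.05 to 1.27 times for a 7-day harm (1.00/0.95 to 1.00/0.79). By 14 days the gap is gone.

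These sizes rest on assumed durations, uniform onset and no recall. Recall shrinks them. Self-drainage without nurse contact would remove or even reverse the gap for those patients.

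A reader might take the whole complication table, including peritonitis, to be inflated against the device. That goes too far. Device-specific items, peritonitis, sepsis, death, events causing admission and the removal criterion are little affected.

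**What to change.** Keep all LTAD safety monitoring and the all-source complication table as planned. Then:

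1. At each existing two-weekly visit, in both arms, use one identical structured complication enquiry covering the preceding two weeks.
2. Record on the eCRF how each event was first found (research visit, nurse visit or diary, hospital, patient report).
3. Beside the all-source table, give a by-arm table of shared harms over the same 12 weeks, limited to events elicited at the common visits, with events leading to unplanned admission in a separate row. Interpret any between-arm difference in mild harms from this table.

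Nurse-found events should not be dropped from reporting, since that could hide real device harm; hence two tables. Routine hospital records should not serve as a neutral common source, because planned LVP admissions give that arm more chances of detection there.

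The cost is one eCRF field, one checklist and one table, with two LTAD counts to report and no extra visits. Two limits remain. A patient may recall an event better because a nurse noticed it, so the bias is reduced, not removed. With 36 of 48 patients recruited by May 2018, the enquiry cannot be added for those who have finished follow-up; for them the source would have to be completed from source data where it was noted.
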